### Data Privacy

Participants will only be identifiable by an anonymous identification number, and all files are stored securely on a server with password encryption. Participant data will only be accessible by the care providers directly assigned to the participant, and anonymized data will be provided to the analysis team members. Participants can withdraw from the study at any point and request that their data be removed from the analysis.

OPTT is compliant with the Health Insurance Portability and Accountability Act, the Personal Information Protection and Electronic Documents Act, and Service Organization Control-2. Additionally, all servers and databases are hosted in the Amazon Web Service cloud infrastructure, which is managed by MedStack to assure all privacy and security regulations are met. OPTT does not collect any identifiable personal information or IP addresses for privacy purposes. OPTT only collects anonymized metadata to improve its service quality and provide advanced analytics to the clinician team. OPTT encrypts all data, and no employee has direct access to participant data. All encrypted backups will be kept in the S3 storage that is dedicated to Queen’s University.

### Ethic Approval

The study was approved (File 6032033) by the Queen’s University Health Science and Affiliated Teaching Hospitals Research Ethics Board in April 2021.

## Results

The recruitment of participants for this study began in May 2021. Participant recruitment has been conducted through social media advertisements, physical advertisements, and physician referrals. To date, 50 participants have been recruited. Data collection is expected to conclude by August 2023, and data analyses are expected to be completed by September 2024, with linear regression analysis (for continuous outcomes) and binomial regression analysis (for categorical outcomes) being conducted.

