**Results:**

The study received ethics approval in April 2021, and participant recruitment began in May 2021. Participant recruitment has been conducted through targeted advertisements and physician referrals. Complete data collection and analysis are expected to conclude by August 2023. Linear and binomial regression (continuous and categorical outcomes, respectively) will be conducted.

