### Outcome Evaluation and Analysis

Participants in both arms will complete the following clinically validated questionnaires at baseline: State-Trait Anxiety Inventory (STAI) [27], Quality of Life Enjoyment and Satisfaction Questionnaire-Short Form (Q-LES-Q-SF) [28], Generalized Anxiety Disorder-7 item (GAD-7) [29], Depression Anxiety Stress Scale-42 item (DASS-42) [30], and a demographic questionnaire. All questionnaires will be completed through OPTT. The STAI, Q-LES-Q-SF, GAD-7, and DASS-42 will be completed again during week 6 and week 12. Using data from previous research incorporating this e-CBT program, a sample of 50 participants in each group was determined to be sufficient for an effect size of 0.5, a power of 0.8, and an α of .05 [31].

Before analysis, the data will be examined for missing, nonsensical, and outlying variables. Missing data will be removed on a per-protocol basis, with a statistical analysis significance level set at .05. Demographic information (ie, age, gender, and race) will be assessed between groups and program noncompleters using independent sample *t* tests. A 2×3 repeated measures ANOVA will be completed for each questionnaire score at the time points to investigate the differences between the 2 groups. An intention-to-treat analysis will be completed to assess whether the outcome of treatment impacts participants’ likelihood of not completing the program. Data will also be assessed with linear mixed-effects models with random effects as patient identification and fixed effects as treatment, time, and their interaction. SPSS (version 24; IBM Corp) will be used for all statistical analyses.

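### The Methods and the Abstract/Results name different, unreconciled analyses; none is primary, and the binomial model has no defined efficacy outcome

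*Protocol article*

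**What the plan says.** Under Outcome Evaluation and Analysis, the Methods commit to two analyses of the same scores. The first is "A 2×3 repeated measures ANOVA will be completed for each questionnaire score at the time points". The second follows two sentences later: "Data will also be assessed with linear mixed-effects models with random effects as patient identification and fixed effects as treatment, time, and their interaction". That section mentions neither ordinary linear regression nor binomial regression.

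The Abstract (Results paragraph) says: "Linear and binomial regression (continuous and categorical outcomes, respectively) will be conducted". The Results section closes in the same way, "with linear regression analysis (for continuous outcomes) and binomial regression analysis (for categorical outcomes) being conducted". Neither mentions ANOVA or mixed models.

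The outcome measures are four questionnaires taken at baseline and repeated: "The STAI, Q-LES-Q-SF, GAD-7, and DASS-42 will be completed again during week 6 and week 12". All are treated as scores, and no responder, remission or cut-off definition is given. The nearest thing to a binary outcome is program non-completion. It appears under an intention-to-treat label, in an analysis meant "to assess whether the outcome of treatment impacts participants’ likelihood of not completing the program", with no model assigned to it.

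The primary objective, under Objectives, is to compare the efficacy of the two programs. No section says which analysis settles that comparison.

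**The concern.** Two parts of the document commit to one set of methods and a third part commits to another. This is a conflict between statements, not detail left to a statistical analysis plan.

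Three things are at stake:

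- **The decisive test is unknown.** A repeated measures ANOVA offers a group effect averaged over visits and a group-by-time interaction. The mixed model offers the interaction or a contrast at one visit. A linear regression would most naturally compare the arms at one visit. These are different hypotheses and can differ in significance on the same data.
- **The choice is open when results are known.** The trial is open-label and every test is set at .05. With no primary analysis named, the most favourable one could be reported as the main result.
- **The binomial model has no stated target.** If it is meant for efficacy, a categorical outcome has still to be prespecified. If it is meant for non-completion, the document does not say so.

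**Working it through.** **Step 1. The statements side by side.**

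| Place | Continuous scores | Categorical outcomes | Primary? |
|---|---|---|---|
| Methods, Outcome Evaluation and Analysis | 2×3 repeated measures ANOVA; also linear mixed model | none named | not stated |
| Abstract, Results paragraph | linear regression | binomial regression, outcome not named | not stated |
| Results section | linear regression | binomial regression, outcome not named | not stated |

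The sample-size sentence does not settle the matter, because it names no test. It gives 50 per group for effect size 0.5, power 0.8 and α .05. A two-sample comparison at one-sided .05 reproduces this: n = 2(1.645 + 0.842)²/0.5² = 49.5, so 50. At two-sided .05, n = 2(1.960 + 0.842)²/0.5² = 62.8, so 63. Sidedness is a separate matter. It is noted only because it explains why the two-sided week-12 comparison below has 70% power and not 80%.

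**Step 2. How much the choice of hypothesis matters.**

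From the document: 50 per arm, three visits, effect size 0.5, α .05.

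Assumed, because the document gives no trajectory or correlation: true differences of 0, 0.25 and 0.5 SD at baseline, week 6 and week 12; equal correlation ρ between visits, from 0.3 to 0.7; two-sided tests; complete data.

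- *ANOVA group effect.* Mean difference = (0 + 0.25 + 0.5)/3 = 0.25. Variance of a participant's mean = (1 + 2ρ)/3. Noncentrality = 0.25/√[(1 + 2ρ)/3] × √(50/2), t with 98 df.
- *Group-by-time interaction.* Centred differences are −0.25, 0 and 0.25, with sum of squares 0.125. Noncentrality = 25 × 0.125/(1 − ρ), F with 2 and 196 df.
- *Week-12 regression, unadjusted.* Noncentrality = 0.5 × √(50/2) = 2.5, t with 98 df, whatever ρ is.
- *Week-12 regression, baseline-adjusted.* Noncentrality = 0.5/√(1 − ρ²) × √(50/2), t with 97 df.

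| Test | ρ = 0.3 | ρ = 0.5 | ρ = 0.7 |
|---|---|---|---|
| ANOVA group effect: noncentrality | 1.712 | 1.531 | 1.398 |
| power | 0.396 | 0.329 | 0.283 |
| Interaction: noncentrality | 4.464 | 6.25 | 10.417 |
| power | 0.451 | 0.596 | 0.826 |
| Week 12 unadjusted: power | 0.697 | 0.697 | 0.697 |
| Week 12 baseline-adjusted: noncentrality | 2.621 | 2.887 | 3.501 |
| power | 0.737 | 0.815 | 0.934 |

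The interaction rows serve both the ANOVA and the mixed model. On complete balanced data, with time as a category and a positive patient variance, the two interaction tests coincide. A check on one simulated data set (50 per arm, three visits) gave F = 7.8537 by both.

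**Step 3. What a binomial model could be applied to.** Among the four questionnaires, nothing is defined as categorical. Gender and race are categorical, but they are baseline variables and are assigned t tests. Non-completion is binary and would suit the model, but the text does not make the link.

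**The case against.** The best defence is that the Abstract and Results are loose summaries of the Methods. A linear mixed model is a regression for a continuous outcome, and an ANOVA and a mixed model can sit in one plan. This stands in part: the methods are inconsistent as written but need not be incompatible. It does not rescue the text. It leaves the ANOVA and the binomial model unexplained in one place or the other, and still nothing is primary.

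Four stronger readings are tempting, and the documents do not support them:

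- *Three models on four questionnaires make 12 separate efficacy tests.* On complete balanced data the ANOVA and mixed-model interaction tests are the same test, so the count includes near-duplicates. No error inflation follows from it.
- *The ANOVA and the mixed model describe different populations.* That is how they usually behave with missed visits. But the Methods place the removal of missing data before all modelling, and read literally this applies to both.
- *No categorical outcome exists.* Non-completion is a binary variable that the plan intends to analyse. What can be said is that no categorical efficacy outcome is defined. A cut-off chosen late is a possibility, not a consequence, and a definition may exist in a fuller document.
- *The power spread measures the difference between the named methods.* Much of it comes from comparing different hypotheses. The highest figures belong to a baseline-adjusted regression that no section specifies.

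**Conclusion.** The point holds as an unreconciled inconsistency in the current text. The Methods name one set of analyses, the Abstract and Results name another, none is primary, and the binomial model has no stated outcome. This rests on the wording alone and needs no assumption.

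The size of the consequence does rest on assumptions: a linear build-up to 0.5 SD, equal correlations and complete data. Under them, power runs from about 28% for the weakest test at its worst correlation to about 93% for the strongest at its best. At ρ = 0.5 it runs from 33% to 82%. Without the baseline-adjusted regression, the range at ρ = 0.5 is 33% to 70%. These figures show only that the choice of hypothesis matters. They do not predict the trial's power.

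The matter should be settled before analysis, because it concerns the test of the primary objective.

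**What to change.** 1. In Outcome Evaluation and Analysis, name one primary analysis before the data are analysed. The mixed model already planned is the natural choice, fitted to all randomised participants with all available visits, with the week-12 between-arm contrast stated as the primary test. The sentence on removing missing data must then be reworded to agree.
2. Label the repeated measures ANOVA a sensitivity analysis, or delete it.
3. Make the Abstract and the Results section name the same analyses as the Methods.
4. Restrict binomial regression to non-completion by arm and say so, or delete it. Keep it for efficacy only if a categorical outcome is prespecified.

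Baseline adjustment is a recommended addition, but it is not needed to remove the contradiction.

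The cost is wording in three places. No new data are needed and there is slightly less analysis to do. The article reports 50 of the planned 100 participants recruited, with analyses still ahead, so at that stage the choice could be fixed without sight of results.

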## Discussion

This study protocol outlines the methods to compare a 12-week e-CBT program and a 12-week check-in program for the management of GAD symptoms. Additionally, the individual effects of each treatment will be evaluated using clinically validated symptomology questionnaires.

GAD is a prevalent mental health disorder that demands resource-intensive interventions to properly address symptoms. CBT is currently one of the first-line treatments for GAD, but it tends to be inaccessible to patients and requires a high level of time commitment from mental health care professionals. Using the internet to deliver mental health treatments has become a promising solution in recent years, with e-CBT being scalable, accessible, and effective in treating GAD [16-18,32-34]. Now that e-CBT is an effective treatment option for patients with GAD, understanding ways to tailor the care to each patient, with varying intensity levels, is crucial for the future of scalability [11,12,16,24-26]. Checking in on patients’ mental health is another form of mental health care that can be less resource-intensive while still offering benefits to patients with GAD. Delivering this electronically and asynchronously would allow for more accessible access to treatment while also providing decreased time commitment, allowing more patients to be helped. There is less research on the impact of a check-in intervention over messaging services, identifying a knowledge gap. By directly comparing this check-in intervention to e-CBT, the efficacy and feasibility of implementing this as a treatment option in a web-based mental health clinic can be investigated. This comparison is original to previous literature, providing a direct comparison between e-CBT and mental health check-ins to investigate whether this is a viable resource to implement in a real-world setting. Most previous literature has investigated the comparison of e-CBT to in-person interventions, treatment groups, medications, or control groups, but none of the sort in this protocol, to the author’s knowledge.

The limitations of this protocol include the lack of a control group. However, the e-CBT program used in this protocol has been previously clinically validated [11], and the main objective of this study is to uncover the differences between these 2 treatment arms. Furthermore, this protocol does not currently include a long-term follow-up, which is something that could be explored in the future.

These findings can provide valuable insight into the effectiveness of a weekly mental health check-in from a care provider versus a validated 12-week e-CBT intervention. If the check-in intervention proves to be a viable and effective option, it could be used as a less resource-intensive option, used in conjunction with e-CBT, or as an option for patients presenting with less severe symptoms. By providing a framework for future research to use these forms of check-in interventions, more work can be done investigating the effects in conjunction with other treatments as well. Electronically delivered mental health interventions are an ever-expanding area with a focus needed on how to continue growing the reach to more patients without sacrificing accessibility and quality of care.

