### Objectives

The primary objective will be to compare the efficacy of an e-CBT program to a web-based mental health check-in program. Additionally, the individual effects of each treatment will be evaluated using clinically validated symptomology questionnaires.

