## Methods

### Study Design

This study will use an open-label randomized controlled trial design to investigate the effects of e-CBT versus a web-based check-in program for GAD. Participants will be randomly assigned, in a ratio of 1:1, to either a 12-week e-CBT program tailored to GAD or a 12-week mental health check-in program to address their symptoms. In addition to these interventions, participants will continue with treatment as usual (ie, lifestyle, family physician appointments, and medications).

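### Neither uncontrolled within-arm change nor a non-significant between-arm difference can show that the check-in program is effective or viable, and e-CBT's earlier validation does not fill that gap

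*Protocol article*

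**What the plan says.** **Aims.** Under Objectives, the primary aim is to compare the efficacy of the two programs. A second aim follows: "the individual effects of each treatment will be evaluated using clinically validated symptomology questionnaires". The Discussion repeats it. The Discussion also says that the direct comparison lets check-in's efficacy and feasibility be investigated, and that it serves to find out whether check-in is a viable resource in real-world care. It then considers possible uses: "If the check-in intervention proves to be a viable and effective option, it could be used as a less resource-intensive option".

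**Design.** "Participants will be randomly assigned, in a ratio of 1:1" (Study Design). Both arms keep their usual treatment, including medication. There is no third arm.

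**Analysis.** Outcome Evaluation and Analysis plans a 2×3 repeated measures ANOVA for each questionnaire, directed at differences between the groups, and linear mixed-effects models with treatment, time and their interaction. On size, it says that "a sample of 50 participants in each group was determined to be sufficient for an effect size of 0.5, a power of 0.8", with α at .05. The article gives no non-inferiority or equivalence hypothesis and no criterion for calling check-in viable or effective.

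**Missing control.** The Discussion states: "The limitations of this protocol include the lack of a control group". It gives two replies: the e-CBT program has been clinically validated, and the main objective is the difference between the arms.

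**The concern.** The article asks two things of the trial: how check-in compares with e-CBT, and whether check-in works well enough to be used. The design addresses the first. For the second, it offers only change from baseline in an arm without a control, and a test of difference against an active program.

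The reply that e-CBT is validated matters because it reads as closing this gap. It would help check-in only if the trial showed check-in to be close to e-CBT, and a test of difference that fails to reach significance does not show that. If the conclusions are not limited in advance, improvement in the check-in arm together with a non-significant comparison could be reported as evidence that check-in is effective, when it is in fact less effective than e-CBT or has no effect beyond usual care.

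**Working it through.** **Inputs from the article:** 50 per arm, 1:1; effect size 0.5, read here as a standardised difference in means (the type is not stated); power 0.8; α .05 (sidedness not stated).

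**Assumptions:** SD = 1, no dropout, a single week-12 comparison and, where adjusted, a baseline to week-12 correlation r = 0.5.

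**1. The article's own figure.** n per arm = 2(z_α + z_0.80)²/0.5².
- One-sided: 2(1.645 + 0.842)²/0.25 = 49.5, so 50. This reproduces the stated size.
- Two-sided, unadjusted: 2(1.960 + 0.842)²/0.25 = 62.8, so 63. Power with 50 per arm is about 70%.
- Two-sided with r = 0.5, variance multiplied by 1 − 0.5² = 0.75: 47.1, so 48. This is also consistent with 50.

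The article does not say which variant was used.

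**2. Precision with 50 per arm.** SE = √(2/50) = 0.20 SD. Half-width = t(.975, 98) × 0.20 = 1.984 × 0.20 = 0.397 SD. If the observed difference were exactly zero, the interval would still allow an e-CBT advantage of about 0.40 SD, which is 0.397/0.5 = 79% of the effect used for sizing. With r = 0.5, SE = 0.20 × √0.75 = 0.173 and the half-width is 1.96 × 0.173 = 0.34 SD.

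**3. Chance of a non-significant two-sided test when e-CBT is truly better.** Approximately Φ(1.96 − d/SE). Unadjusted figures are from the noncentral t and adjusted figures from the normal approximation.

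| True advantage | d/SE, unadjusted | Non-significant | d/SE, r = 0.5 | Non-significant |
|---|---|---|---|---|
| 0.3 SD | 1.50 | 68% | 1.73 | 59% |
| 0.5 SD | 2.50 | 30% | 2.89 | 18% |

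The choice between t and normal moves these by about one percentage point or less.

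**4. What the interval could exclude if the arms were truly equal.** Power = Φ(margin/SE − 1.96). The article gives no margin, so these are illustrations only.
- Margin 0.25 SD: 24% unadjusted, 30% with r = 0.5.
- Margin 0.5 SD: 71% unadjusted, 82% with r = 0.5.
- 80% power without adjustment needs a margin of (1.960 + 0.842) × 0.20 = 0.56 SD, wider than the 0.5 used for sizing.

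**5. Within-arm change.** With 50 in an arm, a standardised change of 0.5 is detected with probability Φ(0.5 × √50 − 1.96) = Φ(1.58) = 94%. Detection is therefore not the difficulty. The expected change is the sum of natural course, regression to the mean, continuing usual treatment and any effect of check-in. With one arm these cannot be separated, and a larger n only estimates the sum more precisely.

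**The case against.** The strongest reply is that the article states no faulty decision rule. Its primary objective and its analysis concern the difference between arms, the missing control is disclosed, and the second reply in the Discussion, that the aim is the between-arm difference, is sound for that aim. The sentence on a viable and effective check-in is conditional. Individual effects are to be evaluated, and no separate within-arm significance test is described. All of this stands, and it rules out several stronger readings that a reader might infer:

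- *That the plan will treat a null result as proof of viability.* No section says so. The gap is that nothing limits the conclusion, while the Discussion asks the comparison to speak to viability.
- *That no result could support check-in.* A result significantly favouring check-in over e-CBT would support it.
- *That sample size is the whole problem.* It bears only on the between-arm route, where 50 per arm could exclude a wide disadvantage. The within-arm problem is one of design.
- *That a null is likely even at the planned effect.* At 0.5 SD it occurs 30% of the time, or about 18% with adjustment. The 68% belongs to 0.3 SD, which is not a figure from the article.
- *That use alongside e-CBT, or in milder cases, needs its own arm or analysis.* These are remarks on possible later use, and need neither.

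What the reply does not answer is the second aim and the first reply on the missing control. Disclosing a limitation does not help when an argument that does not reach the check-in arm is then used to set it aside.

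**Conclusion.** The point holds as a limit on what may be concluded. The stated aim of evaluating each treatment's individual effects, and the use of the comparison to judge check-in's efficacy and viability, go beyond the design unless check-in significantly beats e-CBT. For within-arm change this holds at any sample size and needs no numerical assumption. For the between-arm route, the size is a half-width of about 0.40 SD and a non-significant result in 68% or 30% of trials when e-CBT is truly better by 0.3 or 0.5 SD, falling to about 59% or 18% with adjustment at r = 0.5. These figures assume 50 analysed per arm, a two-sided .05 test and the stated correlation. Dropout would worsen them and a stronger baseline correlation would improve them.

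**What to change.** Amend the wording in four places.

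1. **Objectives and Discussion:** restate the individual-effects aim as a description of within-arm change from baseline that is not attributed to treatment.
2. **Outcome Evaluation and Analysis:** make the between-arm week-12 difference with its 95% CI, adjusted for the baseline score of the same questionnaire, the sole basis for conclusions about check-in relative to e-CBT. The baseline scores are already collected.
3. **Outcome Evaluation and Analysis, and Discussion:** state that a non-significant difference is not evidence that check-in is viable or comparable, and that any such claim will be judged from the size of disadvantage that the interval excludes.
4. **Discussion:** remove the argument that e-CBT's validation offsets the missing control as far as check-in is concerned. The statement that the main objective is the between-arm difference can stay.

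This needs no new participants, arms or measurements. The cost is a weaker permitted conclusion after a null result: with 50 per arm the interval may exclude only a fairly large disadvantage, and the report would have to say so.
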